### 3.4 Moments of evaluation

The evaluation will assess the capacity of the course to turn students into ambassadors that can change the framework of the discussion in society. We understand as ambassadors the students who demonstrate: (1) an adequate degree of understanding of the concept of palliative care, (2) a positive attitude towards the social problem, (3) the ability to communicate the message of palliative care and (4) to retain the knowledge five months after taking the course. The overall assessment of the course will focus on four moments of evaluation (Fig 3).

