#### 3.4.3 Moment 3: Final assessment

The final two classes in the course contemplate a seminar where students will learn the basics of Rhetoric. They will write a speech, applying the knowledge of palliative care acquired during the course and the resources given throughout the seminar. The speeches will be sent to and graded by the professor, who will forward them to the research team to be analyzed accordingly. The teacher will then proceed to select the five best speeches for a Message Transmission Experiment. For this experiment, five selected students will deliver their speech in front of first-year students not enrolled or related in any way to the course. Following the speeches, the first-year students will fill out a questionnaire to assess their understanding of palliative care after the experience.

Additionally, prior to the last day of class, students will turn in a written reflection regarding the Module III experience. This material will also be analyzed for the research with the prior written consent of the students. After the class is over, students will receive the link to answer the last PCKQ and TECA. Participants will also receive a link to provide feedback on the course through a satisfaction and commitment questionnaire that includes an open question and a learning commitment regarding an attitude change: "After what you have learned in this course, what do you intend to change in your attitude in the coming months to enhance the palliative care message?".

Lastly, all the students and teachers of Care and Society will be invited to participate in a focus group to evaluate the overall experience in this course. The first five students who respond to this request will be selected. The purpose of this focus group is not to evaluate the knowledge of the participants, but to discuss the strengths and weaknesses of the methodology, the content and other aspects of the course. The focus groups will later be transcribed, and thematic content analysis of the material will be carried out.

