### 3.5 Data management

To protect the identity of the participants, every student will create his or her own code at the beginning of the study. The code will be the combination of a city and three numbers. It will be used in all questionnaires, so that the researcher is only be able to associate each questionnaire with a code instead of data identifying the sender.

Students will receive the first set of questionnaires in an email invitation sent through the university’s in-house platform. The email addresses of the students who decide to participate will be saved by the researchers to send the next steps of the study directly to them. These emails will be stored separately and will in no way be linked to the answers of the questionnaires or to the generated codes.

The answers of the questionnaires will be analyzed after the course has been completed and the grades submitted. This guarantees that professors will not receive any information related to the study. Written consents about the contact will be destroyed once the project is finished and will not be associated in any way to the answers of the questionnaires. All information will remain confidential in accordance with the Data Protection Act.

The data from this study will be incorporated into a database or file without personal data and access will be available to the study personnel. A backup copy of the personal data file related to recruited participants will be kept on the hard drive of the principal investigator’s university computer equipment and will be accessible to the principal investigator for 3 years. After those three years, all data will be deleted.

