## 4. Preliminary results

The first edition of Care and Society took place from January to May 2022. The course had 29 students enrolled. For the preliminary results, we compared the PCKQ answers of the participants throughout the course. We also assessed the results of the Message Transmission Experiment, and we obtained an initial overview of the recurring themes of the focus group.

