### 4.1 Palliative Care Knowledge Questionnaire

The students were asked to complete a PCKQ in three different moments of the course: before it started (Moment 1), after the first module (Moment 2), and during the last class (Moment 3). The PCKQ included four multiple choice questions with multiselect answer options, in which students were asked to pick the options that best described palliative care, and one open question in which students were asked to define palliative care. From the 25 students that accepted to participate, 12 students responded in Moment 1, 25 responded in Moment 2 and 21 responded in Moment 3.

The analysis carried out is centered on the open question and only took into consideration respondents who answered at the 3 Moments (S1 File). Although some of the students appear to have a vague knowledge on palliative care, when asked to define palliative care in Moment 1, the answers revolved around the idea of the final moments of the patient. The definitions made use of concepts such as “terminal”.

“The care and support received by terminally ill patients and their families”,P1.“It is a treatment that is carried out in very specific and extreme circumstances to provide the patient with a state of well-being and tranquility, avoiding the pain without cure”,P2.“Accompanying terminally ill people”,P3.

In Moment 2, we start to see a shift in perspective. While students still made use of words like “terminal” in the definitions, the answers were no longer focused on that topic. The ideas of reducing the pain and suffering, enhancing the life quality, and accompanying and caring for the patient were present in most of the answers.

“Palliative care is the support, help and assistance given to patients in advanced diseases with near-death expectation, so that they have a better quality of life and comfort, and their suffering is reduced”,P1.“Palliative care is a treatment for chronic illnesses or those with a life expectancy of less than 6 months, which helps the patient to reduce pain and give them a better quality of life”,P2.“Caring to reduce the suffering of a person who is terminally ill”,P3.

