### 4.2 Message Transmission Experiment

During the last class of the course, five students were selected to read out loud their speech in front of their classmates and two guests. The guests were two first-year students not enrolled in the course, who have previously display little or no knowledge regarding palliative care in an assignment delivered for another university course. After hearing all the speeches, they were asked to define palliative care (S2 File). One of them defined palliative care as "a medical treatment intended for patients with a terminal illness with the aim of reducing their suffering as much as possible". The other one wrote that palliative care "is a special care that focuses on people who do not have the possibility of being cured of their illness. They try to support, both focused on the disease and psychological consequences, to the patient and the family".

Two lessons can be drawn from this experience. The first one is that the students were able to learn the basics of rhetoric from the four-hour seminar. The speeches written for the experiment were well structured and clearly expressed the concepts that the students had learnt during the course. The second one is that the speeches showed signs of being effective in conveying the concepts learnt throughout the course to the guests. The guests, who presumably knew little or nothing about palliative care prior to the experience, provided an acceptable definition of palliative care after hearing the speeches. Thus, the students of the course showed their ability to communicate and retransmit the palliative care message to their peers.

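### The only recipient-based test of ambassador criterion 3 uses the five best speeches and one pooled response, so it scores no individual student and cannot represent the class

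*Protocol article*

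**What the plan says.** Section 3.4 sets the target at the level of the student: "We understand as ambassadors the students who demonstrate: (1) an adequate degree of understanding of the concept of palliative care", followed by a positive attitude and then "3) the ability to communicate the message of palliative care and (4) to retain the knowledge five months after taking the course". No particular instrument is attached to the third criterion.

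Section 3.4.3 has every student write a speech. The professor grades the speeches and passes them to the research team for analysis. The teacher then chooses the five best for the Message Transmission Experiment, in which "five selected students will deliver their speech in front of first-year students not enrolled or related in any way to the course". The listeners complete a questionnaire after the speeches.

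Section 4.2 reports how this was done in the pilot. There were two guest listeners, and "After hearing all the speeches, they were asked to define palliative care". The section concludes that the students of the course had shown they can communicate and pass on the message to peers.

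Section 3.5 says of the self-made study code: "It will be used in all questionnaires, so that the researcher is only be able to associate each questionnaire with a code". It adds that email addresses are stored apart and are not linked to codes or answers. It does not say how speeches or interviews are labelled.

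**The concern.** A claim about criterion 3 can be made at two levels: for a given student, or for the class. The experiment supports neither.

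- **Individual level.** The listeners answer once, after five speeches. A good definition could come from one clear speech, from repetition across all five, or from what the listener already knew. Nothing in the response separates the speakers.
- **Class level.** The five are the top of the teacher's ranking, not a sample of the class. What the best speeches convey says little about the rest, and selection of this kind favours a positive result.

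At stake is how the pilot is read. Section 3.2 says the pilot serves to improve the course and its assessment techniques before use at other universities. If the experiment is carried forward as the evidence on communication, each later edition will produce the same selected, unattributable result.

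**Working it through.** The article states no sample size calculation, power or target rate for this assessment, so there is no figure of its own to reproduce. The check is a count plus a comparison of sections.

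**Inputs**
- Enrolled: 29 (Section 4: "The course had 29 students enrolled").
- Accepted to participate: 25 (Section 4.1: "From the 25 students that accepted to participate, 12 students responded in Moment 1, 25 responded in Moment 2 and 21 responded in Moment 3").
- Speakers: 5, chosen as best (Section 3.4.3).
- Listeners in the pilot: 2, one definition each, after all speeches (Section 4.2).

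**Students outside the recipient test**
- Of those enrolled: 29 − 5 = 24, and 24/29 = 82.8%. The speakers are 5/29 = 17.2%.
- Of those who accepted: if all five speakers were participants, 25 − 5 = 20, and 20/25 = 80.0%. The article does not say whether they were. Any speaker outside the 25 raises the count, so 20 is a minimum.

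**Recipient-based scores that belong to one student**
- Outside the test: none, because these students did not speak to the guests.
- Among the five speakers: none, because each guest gave one answer covering five speeches.
- Total: 0 of 29.

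**Conclusion set against evidence.** Section 4.2 moves from five selected speeches and two listeners to a statement about the course's students as a group. The Conclusion of the Abstract likewise credits the students without restriction. Section 7 is narrower and speaks only of some of the students, but then lists, among the results hinted at so far, that the students have begun communicating with peers.

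**Linkage.** Understanding (criterion 1) and retention (criterion 4) are assessed by questionnaires, which carry the code. Speeches reach the researchers through the grading professor, and interviews follow an emailed invitation. No code is stated for either. Section 6 reports that some students had difficulty remembering their codes and some chose identical ones, so that answers had to be excluded. Even the stated linkage was therefore fragile.

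**The case against.** The strongest reply is that criterion 3 is not tied to the experiment. Section 3.4 asks for an ability, not for measured understanding in a listener. All written speeches go to the research team for analysis. The Moment 4 questionnaire asks for an example of how the learning commitment was carried out, and the interviews ask whether the message was passed on. Section 7 says that judging ambassador status still requires analysis of the course material and the mid-term results, and that the assessment of message transmission needs more work.

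Most of this stands, and it limits the point. A reader might infer that the 24 students who did not speak cannot be scored on criterion 3 at all. The documents do not support that: they lack a recipient-based score, but other student-level material is planned. A reader might also infer that a planned proportion of ambassadors has become impossible to calculate. No such proportion, and no joint rate over the four criteria, is a stated endpoint. Nor is the absence of a scoring rubric from the article a fault, since the full protocol may hold one. The linkage point rests partly on silence, so it supports only that linkage is not assured, not that it is impossible.

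The reply does not reach the stated features of the test: selection of the best five and a single response after all the speeches. A rubric held elsewhere would change neither. Interviews are voluntary and self-reported, and they show whether retransmission took place rather than how well a student can communicate. The remedy named in Section 7, better assessment of the recipients' prior knowledge, addresses neither selection nor pooling.

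**Conclusion.** The point holds in a limited form. The Message Transmission Experiment is the only recipient-based evidence on criterion 3. As planned and as carried out, it yields no individual score (0 of 29) and cannot represent the class, because at least 20 of 25 participants (80.0%), or 24 of 29 enrolled (82.8%), are outside it and those inside were chosen for quality. The group-level conclusion in Section 4.2 is not supported by this test. The other planned evidence could fill the gap, but joining it to a student's knowledge and retention results is not assured.

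This rests on two readings: that the questionnaire after the speeches is a single one, which Section 4.2 bears out for the pilot, and that the 25 who accepted are among the 29 enrolled. It is a worthwhile improvement to the assessment and a correction to one conclusion. It does not invalidate the evaluation.

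**What to change.** 1. Assess criterion 3 for every consenting participant from the written speech already submitted. Use one fixed content rubric (accuracy of the concept, clear structure, message understandable to a lay peer). The research team should apply it without sight of the grade or of selection for the experiment, so raters should score before the experiment or not attend it.
2. Put a study code on the research copy of the speech and keep the name off it. Replace the self-made code with a more reliable one, for example a unique issued code that the student can recover without the researchers learning who holds it.
3. Report the Message Transmission Experiment as illustrative only. Limit the conclusion in Section 4.2, and the matching sentence in the Abstract, to the five selected speeches taken together.

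The cost is one rubric, a change of code system, and the scoring of at most 25 short texts (one per student who accepted) that are already collected and due for analysis. For the pilot edition, the speeches can still be scored for the class, though linking them to questionnaires afterwards may not be possible. The downside is that a rubric applied to a text measures communication less directly than a listener's response.

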#### 3.4.4 Moment 4: Mid-term assessment

Five months after the publication of course grades, students will be emailed a link to an online questionnaire to assess their mid-term knowledge and to indicate the extent to which they have implemented the learning commitment outlined in the satisfaction and commitment questionnaire. Students should respond to the question “You have set out to change your attitude to improve the palliative care message. Have you managed to accomplish this in the last few months? Please provide an example.” Furthermore, they will receive an invitation to participate on in-depth interviews to talk about their experience on the months following the course and to confirm whether they have retransmitted the palliative care message at some point during that timeframe.

The 5-month timeframe was selected taking into consideration that the course grades will be made public in early June. Hence, we will be recontacting students no sooner than in November of 2022. Thus, by the time we recontact the students, some of them will be finishing their second-to-last semester in university. This is significant for two reasons. First and foremost, the recontact form they received in the Moment 1 of evaluation allowed communication via their university email. If we wait longer, some of the emails may become inoperative. Secondly, sending invitations with a semester’s leeway allows us to have plenty of time to schedule interviews knowing that the students are still in the same geographic location, facilitating face-to-face interviews or at least with similar schedules to ours.

### 3.5 Data management

To protect the identity of the participants, every student will create his or her own code at the beginning of the study. The code will be the combination of a city and three numbers. It will be used in all questionnaires, so that the researcher is only be able to associate each questionnaire with a code instead of data identifying the sender.

Students will receive the first set of questionnaires in an email invitation sent through the university’s in-house platform. The email addresses of the students who decide to participate will be saved by the researchers to send the next steps of the study directly to them. These emails will be stored separately and will in no way be linked to the answers of the questionnaires or to the generated codes.

The answers of the questionnaires will be analyzed after the course has been completed and the grades submitted. This guarantees that professors will not receive any information related to the study. Written consents about the contact will be destroyed once the project is finished and will not be associated in any way to the answers of the questionnaires. All information will remain confidential in accordance with the Data Protection Act.

The data from this study will be incorporated into a database or file without personal data and access will be available to the study personnel. A backup copy of the personal data file related to recruited participants will be kept on the hard drive of the principal investigator’s university computer equipment and will be accessible to the principal investigator for 3 years. After those three years, all data will be deleted.

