## 6. Limitations

When launching the pilot, we decided not to have a control group. The two main reasons were: we did not consider the experience of a student taking Care and Society to be comparable to that of a student taking any other subject of the Core Curriculum offerings. And, secondly, the questionnaires themselves could lead to bias. By taking the same questionnaire repeatedly, it could generate curiosity in the control group participants, who might be able to acquire palliative care knowledge on their own and improve their performance in the following questionnaires. Nonetheless, for future attempts, we believe that the existence of a control group is advisable to rule out external change factors, such as exposure to news about the topic or to other media outlets.

The code system is another variable to take into consideration. As there is a time frame superior to a month in between moments of evaluation, some of the participants had a hard time remembering the city and the numbers they chose at the beginning of the pilot study. Furthermore, some of the participants chose the same city and the same combination of numbers. As a result, some of the answers had to be excluded from the preliminary results. In future attempts, a new system of codes might be helpful to improve the data recollection.

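### The self-chosen code is the only link between a student's questionnaires, it failed for some students, and no remedy is described before the five-month assessment

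*Protocol article*

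**What the plan says.** Section 3.5 (Data management) sets up the link. At the start, "every student will create his or her own code at the beginning of the study", and "The code will be the combination of a city and three numbers". The code goes on all questionnaires so that "the researcher is only be able to associate each questionnaire with a code instead of data identifying the sender". E-mail addresses are kept for sending later steps, but they "will in no way be linked to the answers of the questionnaires or to the generated codes".

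Section 6 (Limitations) reports how this worked. With more than a month between moments, "some of the participants had a hard time remembering the city and the numbers they chose at the beginning of the pilot study", and "some of the participants chose the same city and the same combination of numbers". Some answers were therefore left out of the preliminary results. The article suggests that a new code system might help in later editions.

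Section 3.4 (Moments of evaluation) defines ambassadors as students who show adequate understanding, a positive attitude, the ability to communicate the message, and the capacity "to retain the knowledge five months after taking the course". Section 3.4.4 places Moment 4 five months after grades are published. Section 7 says that the mid-term results are needed to judge whether students became ambassadors.

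**The concern.** The ambassador definition is a conjunction within one person. To apply it, a student's knowledge and attitude answers, evidence of communication, and Moment 4 answers have to be joined. Between questionnaires, only the code can do that. When a code is forgotten, the separation of e-mails from codes leaves no described way back. When two students share a code, their answers can be paired with each other. The risk is greatest when one of them answers at one moment and the other at the next, because the duplicate is then invisible and a difference between two people is read as change in one.

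Forgetting already occurred over intervals of somewhat more than a month. Moment 4 comes after a longer interval, and the article describes no change to the code for this cohort before then.

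**Working it through.** The article gives no count of failed codes and no size for the matched set, so there is no figure of its own to reproduce. The checks below give bounds and scale.

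**Inputs from the article.** 29 students enrolled (section 4). Of 25 participants, 12, 25 and 21 answered at Moments 1, 2 and 3 (section 4.1). The analysis of the open question used only those who answered at all three.

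**1. How many could be linked with a perfect code?**
- Moments 1 to 3, lower bound: 12 + 25 + 21 − 2 × 25 = 8.
- Moments 1 to 3, upper bound: min(12, 25, 21) = 12.
- So 8 to 12 of 25 (32% to 48%) before any code loss. This limit comes from Moment 1 non-response, not from the code.
- Moment 3 to Moment 4: up to 21, the number who answered at Moment 3. The four ambassador criteria are attained states and none needs a baseline, so 21 is the relevant ceiling for that status.

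**2. Is the format itself too small?** Read three numbers as three digits (assumption), so that K = 1000 × number of cities, and let choices be uniform. For n = 25, P(at least one duplicate) = 1 − ∏(1 − i/K), i = 0 to 24.

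| Equally likely cities (assumed) | K | P(duplicate) |
|---|---|---|
| 1 | 1,000 | 26% |
| 5 | 5,000 | 5.8% |
| 10 | 10,000 | 3.0% |
| 50 | 50,000 | 0.6% |

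People do not choose uniformly. If one popular code has probability q, then P(two or more of 25 share it) = 1 − (1 − q)^25 − 25q(1 − q)^24. For assumed q = 0.03, 0.10 and 0.15 this is 17%, 73% and 91%. Free choice is therefore the weak point more than the number of possible codes. The reported duplicates settle that the problem is real; these figures only explain it.

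**3. What might imperfect recall cost?** Let r be the chance that a student gives a matching code at a later moment (assumption). Suppose no other dropout.

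| r | 12 starters matched through Moment 3: 12r² | 21 respondents matched from Moment 3 to 4: 21r |
|---|---|---|
| 0.95 | 10.8 | 20.0 |
| 0.90 | 9.7 | 18.9 |
| 0.80 | 7.7 | 16.8 |
| 0.70 | 5.9 | 14.7 |

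Both columns are upper figures for the given r, because non-response at later moments would lower them further.

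**The case against.** The strongest reply is that the authors disclose all of this. Section 6 names both failures and their consequence, and section 3.2 says that the pilot exists partly to improve the assessment techniques before use in other universities. That stands as a matter of candour. It does not repair the link: the limitation points to later editions, while this cohort's Moment 4 is treated as still to come.

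Several stronger readings are tempting, and the article does not support them.
- A reader might infer that pairing failed altogether. Section 6 says only some participants and some answers, and section 4.1 does analyse respondents from all three moments.
- A reader might take 12 as the ceiling for ambassador status. It limits baseline comparisons only; up to 21 can enter a Moment 3 to Moment 4 link.
- A reader might treat ambassador status as the primary endpoint. None is named, and no per-student count or proportion is specified.
- A reader might suppose that speeches reach the research team under students' names, or that interview records carry no code. Sections 3.4.3 and 3.4.4 are silent, and a condensed article may leave such labelling to the full protocol.
- A reader might assume that less engaged students forget more, so that the loss is selective. This is plausible, but nothing in the article shows it.
- A reader might hold that the Moment 4 question on attitude change is useless without a match. It is a self-report that can be read alone, although matching it to the Moment 3 commitment would strengthen it.

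**Conclusion.** The concern holds in a limited form. The self-chosen code is the only described link between a student's questionnaires, it has no uniqueness check or recovery route, and by the authors' own account it failed for some students. Because ambassadors are defined student by student and the definition includes retention at five months, the status cannot be assembled for every student. It can still be assembled for those whose codes match.

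The size of the loss is unknown because the number excluded is not reported. With assumed recall of 0.70 to 0.95, and all 21 Moment 3 respondents answering again, 21 − 14.7 = 6.3 down to 21 − 20.0 = 1.0 of them would be unlinked on average. This range rests on the recall assumption alone and is not an estimate from the data. Disclosure as a limitation does not remove the problem, since a better method is available that keeps the confidentiality commitment.

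**What to change.** **Later editions.** Replace the free-choice code with one that the student can rebuild each time from several stable personal facts that do not readily identify anyone. Such a code is not unique by construction: by the table above, 1,000 equally likely values still give a 26% chance of a duplicate among 25. So check for duplicates at Moment 1, and again at first entry for those who start later (25 − 12 = 13 participants did not answer the Moment 1 questionnaire in the pilot). Ask one reserve item at every moment to separate any duplicates. Ask for the same code on the research copies of speeches and reflections, the satisfaction form, the Moment 4 questionnaire and the interview sheet.

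**Current cohort.** Remind students of the code format in the Moment 4 invitation. Ask them to restate their Moment 3 commitment as a secondary match. Keep answers with unmatched or duplicate codes in unpaired per-moment summaries, and report how many could not be linked at each moment.

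**Two alternatives to avoid.** A token sent with each e-mail invitation would tie addresses to answers and break the separation promised in section 3.5. Stable facts first collected at Moment 4 cannot link back, because no earlier questionnaire is described as recording them.

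**Cost.** A few extra form fields, an ethics notification, and slightly weaker anonymity, which matters in a class of 29 and should guide which facts are chosen. E-mail addresses stay unlinked as promised.
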